## Abstract

**Background:**

Children born to mothers who experience social complexity (e.g. substance misuse, intimate partner violence, mental ill health, a history of maltreatment) are at increased risk for a range of adverse outcomes at birth and during development. Home visiting programmes have been advocated as a strategy for improving outcomes for disadvantaged mothers and children, such as the Nurse-Family Partnership for young, socially disadvantaged first-time mothers. However, no evidence-based programme is available for multiparous women or older first-time mothers. The New Baby Programme was developed in Northern Ireland. It augments the universal health visiting service available in the UK with a content designed to promote maternal health and well-being in pregnancy, maximise secure attachments of children and parents and enhance sensitive parenting and infant cognitive development.

**Methods/Design:**

This pilot study is designed to investigate whether it is possible to recruit and retain socially vulnerable mothers in a randomised trial that compares the effects of the New Baby Programme with standard antenatal and postnatal care. Feasibility issues include the referral/recruitment pathway (including inclusion and exclusion criteria), the consent and randomisation, the ability to maintain researcher blinding, the acceptability of the intervention to participants, and the feasibility and acceptability of the outcome measures. The results of the study will inform a definitive phase-3 RCT.

**Discussion:**

Trials of complex social interventions often encounter challenges that lead to the trial being abandoned (e.g. because of problems in recruitment) or present considerable analytic challenges relating to dropout, attrition and bias. This pilot study aims to maximise the chances of successful implementation.

**Trial registration:**

ISRCTN35456296 retrospectively registered

## Background

Social circumstances may adversely affect the outcomes of pregnancy, both for women and their baby [1]. *Saving Mothers Lives* documents the increased risk of death during or after pregnancy of socially disadvantaged or excluded women in England and Wales [2]. Of the women who died, those with socially complex lives were less likely to contact maternity services early or to stay in regular contact. Compared with women who booked before 20 weeks into their pregnancy, those who booked late or missed more than four regular appointments were more likely to be black African or Caribbean, experiencing domestic abuse, misusing substances, known to child protection services, or unemployed [3].

*Perinatal Mortality* (2009) highlighted the disparity in rates of stillbirth and neonatal death between white women and those from ethnic minority groups in the UK [4]. Unemployment, socioeconomic deprivation, ethnicity (African and African Caribbean, Indian and first-generation migrants from Pakistan) and later antenatal booking appointments (past 13 weeks) are all associated with increased risk of stillbirth [2, 5, 6]. Complex social factors may enhance stress, now recognised as deleterious to the health of both mother and child [7, 8].

Children born to mothers whose circumstances feature social complexity are at increased risk of a range of adverse outcomes, including birth outcomes (e.g. low birth weight, preterm delivery), health problems in infancy and impaired development. Some of these are associated with poor maternal health during pregnancy and/or behaviours that can adversely impact on the developing child. Key concerns include smoking [9], substance misuse [10], intimate partner violence [11], mental ill health [12, 13], socio-economic deprivation and a history of maltreatment [14, 15].

Despite a small reduction in inequality of pregnancy outcomes between the most deprived and better off women in the UK population [16, 17], the problem remains a significant one, with serious implications for the many children living with parents coping with social complexities.

### Home visiting programmes

Home visiting programmes have been advocated as a strategy for improving the health of disadvantaged children, and in 2006, the prime minister, Tony Blair, identified home visiting programmes as an ‘early intervention’ that could help combat social exclusion [18]. Unlike universal health visiting, home visiting programmes often start antenatally and may continue for 2 years postpartum. Typically, they involve structured visits by those experienced in child health and development. Some programmes use professionals as home visitors (on the grounds that parents value ‘expert’ and ‘confidential’ advice and support), whilst others use trained and supervised lay visitors (on the grounds that those who have ‘been there’ are better able to engage those who are experiencing difficulty). Home visiting programmes may target maternal smoking, poor attachment, poor nutrition, the under-stimulation of children, lack of social support and a range of factors known to increase risk for maltreatment [19–23]. They may seek to improve the economic status of families by helping mothers complete their education, secure employment and plan for any future pregnancies [24].

Home visiting programmes are often designed specifically to engage women who are traditionally found ‘difficult to engage’ by routine services. Intervention takes place within the home because this is where most parenting takes place. As well as providing natural opportunities to model, practice, and reinforce good parenting, home visiting maximises the chances of parental engagement. Reduced caseloads enable staff to visit more frequently to be available between scheduled visits and to provide a wider range of support services, such as help with practical tasks (e.g. arranging and keeping appointments with other agencies, negotiating with welfare agencies, general advocacy). Staff usually receive additional training in order to deliver these programmes. This may include enhancing their understanding of the wider context of parenting (e.g. how childhood maltreatment or mental health problems can influence parenting) and developing skills associated with enhancing parental engagement (e.g. motivational interviewing).

### Nurse-Family Partnership (NFP)

NFP is based on a number of psychological theories, such as theories of cognitive development [25], attachment theory [26] and social learning theory [27, 28], organised within an ecological framework. NFP operates on the understanding that successful programmes must be able to make significant impacts on ‘the enduring environment in which the family is functioning’ [29] (p.12). The programme assumes that new parents are committed to the well-being of their child and that most will act in ways they deem to be appropriate during pregnancy and subsequent years. Failures of parenting are therefore assumed to reflect a lack of knowledge about what their children need or to arise from other factors such as mental illness or life stressors. NFP is targeted solely at first-time mothers on the basis that it is at this point that mothers are maximally motivated to engage in behaviour change to promote the well-being of their child.

NFP has been evaluated in three randomised trials, in three locations in the USA. Each sample was different, but all were socially disadvantaged. Outcomes and measures differ across the three trials, and the programme developers were responsible for these three evaluations (and have been involved in the small number of more independent evaluations). Generally, the three trials were well designed and implemented and indicate positive impacts in a range of maternal and child outcomes. However, recent trials have found no evidence of impact in the UK [30, 31]. NFP has been commissioned for use within the UK, where it is known as the Family-Nurse Partnership (FNP). As a licenced programme, the cost is considerable, and there is currently no comparable provision for the significant numbers of older and/or multiparous mothers presenting with complex social factors. The New Baby Programme (NBP) aims to bridge this gap.

### The New Baby Programme

The NBP was developed within the South Eastern Health and Social Care Trust in Northern Ireland. It aims to promote maternal health and well-being in pregnancy, maximise secure attachments and enhance sensitive parenting and infant cognitive development. In setting these aims, the programme drew on evidence concerning the importance of maternal health and well-being in pregnancy for optimal in utero development (e.g. [32–36]) and the importance of secure attachments [37–40] and ensuring healthy social and emotional development in the early years [8, 41, 42].

Exposure to the same stressor does not necessarily lead to the same outcome for all who experience it (multifinality). Similarly, there are many paths to the same type of outcome (equifinality). Consequently, interventions such as home visiting are necessarily broad-brush in some respects. Promoting optimal prenatal health will require a different strategy for a mother who does not smoke or drink than one who does; it will look different for a mother who is homeless than one who is not, and so on. The logic model underpinning the NBP reflects this complexity (see Fig. 1). The programme seeks to combine a core curriculum of evidence-based advice, information and interventions with the opportunities and flexibility afforded to health visitors with small caseloads, additional training and specialist supervision.

**Fig. 1 Fig1:**
[figure not shown]
Logic model

A service evaluation of the NBP, conducted in 2013, identified the programme as a promising intervention, well received by staff and parents, but needing further work to describe and manualise the intervention and to more tightly specify the training and supervisory needs of those delivering it. This work has been undertaken. The Public Health Agency in Northern Ireland wishes ultimately to secure an independent evaluation of the programme using a randomised controlled trial (RCT). The primary objective of an RCT would be to determine whether the NBP, compared with routine antenatal and postnatal care, can improve infant attachment and maternal sensitivity among pregnant women with complex social factors and the quality of maternal-child relationships. The secondary objectives would be to determine whether the NBP can improve maternal mental health and outcomes for children, at birth and during the first year of life.

### Aims of the study

This pilot study is designed to test the feasibility of an RCT to investigate the effectiveness of the New Baby Programme for pregnant women of any age presenting with socially complex circumstances. It will determine the recruitment and retention rates required, the process of randomisation, the procedures for masking allocation status from the research team and the acceptability of both the intervention and participation in the study. Particular attention will be paid to the feasibility and acceptability of the outcome measures used, as these require video-taping of mothers and babies, one of which will entail attendance at a clinic.

### Research questions

The research questions for the study are as follows:Is the study design feasible? Is it possible to recruit and retain women with socially complex circumstances into an RCT and collect data at 20 weeks of gestation and then when infants are 2, 6 and 12 months old?Is the intervention acceptable to participants and do they engage with it?Are the proposed outcome measures acceptable to participants and are they willing to collaborate in providing the required data?How many participants will be needed for a sufficiently powered RCT, and what time frame will be needed for recruitment?

#### Primary outcomes

1. Recruitment as a percentage of eligible participants

2. Retention assessed by percentage of participants randomised for whom data are available at baseline and 2, 6 and 12 months postpartum

#### Secondary outcomes

3. Acceptability of trial randomisation and data collection

4. Ability to maintain researcher blinding

5. Acceptability of the intervention and comparator

6. Acceptability of the outcome measures

## Methods/Design

### Design

This study comprises a pilot randomised trial in which eligible women are allocated to either the New Baby Programme or standard care. The social circumstances of the population targeted are such that recruitment and retention may be particularly challenging, so the study includes a qualitative component designed to provide information about the acceptability of the trial processes to participants and other key stakeholders (e.g. midwives, social care professionals, and GPs).

### Participants

In total, we aim to recruit 50 women with socially complex circumstances presenting for antenatal care at the Ulster, Ards and Bangor Hospitals (County Down) in the South Eastern Health and Social Care Trust in Northern Ireland. Twenty-five women will be randomised to receive the New Baby Programme. The remaining 25 women will receive Universal Core Programme recommended in the Healthy Child Programme through midwifery and health visiting services. This is the routine package of care that will be offered to those who do not wish to take part in the randomised trial. We aim to recruit the target sample of 50 participants over a 10-month period (Fig. 1).

#### Inclusion criteria

Participants will be eligible for the study if they are first time pregnant women over 19 years of age or multiparous women of any age (with a gestational age less than 18 weeks) presenting with one or more of the following: (i) social isolation/low family support/father in prison; (ii) intimate partner violence; (iii) substance misuse; (iv) maternal stress or history of mental ill health; (v) current involvement with social services or probation; (vi) history of care or a care leaver; (vii) and abnormal reaction to pregnancy.

#### Exclusion criteria

Women will be excluded if they do not meet any of the inclusion criteria of risks factors for social complexity and/or if they are under the age of 12 years or they are unable to speak sufficient English to take part in the intervention arm (identified as difficulty reading patient information sheets).

Midwives will use a screening tool (in the form of a vulnerability checklist) at the 8–18 weeks booking-in visit to determine women’s eligibility for the study.

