### Recruitment and informed consent

Recruitment will be undertaken via midwives at the three participating hospitals. Eligibility for the study will be determined by midwives who will use a screening tool (in the form of a vulnerability checklist) at the 8–18 weeks booking-in visit. They will briefly inform all eligible women about the study and invite them to take part. They will also provide eligible mothers with accessible, written information and inform them that a specialist nurse may telephone them to provide more details of the study. A senior nurse (a trust manager) from the Ulster Hospital will then telephone mothers to confirm eligibility and establish if the pregnancy is still viable. Women who are not eligible will be thanked for their time. The specialist nurse will ask eligible mothers if they would be interested in taking part and, if so, whether they are willing to be contacted by a named researcher (details of all members of the research team will be included on the information sheet). If the eligible mother is still interested in taking part and is willing for her contact details to be passed to the trial manager, then one of the specialist nurses will contact the research team.

One week following their booking-in visit, a researcher will contact the eligible mother to confirm if she is still willing to take part and, if so, to arrange a suitable time to visit her at her home. During this visit, the expectant mother will be asked to sign a consent form and baseline data will be collected.

During the baseline visit, the researcher will explain the study, including the possibility of any woman receiving the New Baby Programme (NBP) or Management as Usual (MAU), and how this will be determined (i.e. randomisation by a third party not directly involved in the study). In part to recognise their contribution to the study and to encourage retention, participants will be given a £20 gift voucher at completion of each data collection (baseline and 2, 6 and 12 months postpartum) and on completion of the Strange Situation Procedure [55].

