Overall, response cards will be used for questions that provide a number of response options. All data will be collected during face-to-face interviews in the woman’s home, unless otherwise requested. In the event of respondents having low levels of literacy, the researcher will administer questions orally.

Outcome measures targeted by the intervention will be collected at baseline and 2, 6 and 12 months. Whilst the sample size in this pilot study is not sufficient to inform the power calculations that will be required for a phase 3 study, we will use the available data to estimate the standard deviation and interval estimates (i.e. 95% confidence intervals) of the outcome measures, as this will help inform those calculations (see NIHR guidance on feasibility studies).

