### Study outcome measures

#### Primary outcomes—recruitment and retention rates

We will use the screening tools completed by midwives and the records of the senior nurse (see above) to estimate the number of women eligible for the trial and the percentage recruitment rate. Retention of participants will be determined via those for whom data are available at each data collection point. These data will address the feasibility (can we recruit and retain participants) and design (duration, number of recruitment sites required) of any future RCT.

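### The spoken-English exclusion is identified by a reading test, so fluent women with low literacy can be excluded and their place in the recruitment denominator is unclear

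*Protocol article*

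**What the plan says.** Under Exclusion criteria, the protocol article excludes women who are "unable to speak sufficient English to take part in the intervention arm (identified as difficulty reading patient information sheets". The parenthesis is the only method given for identifying these women. The same section describes the eligibility instrument: "Midwives will use a screening tool (in the form of a vulnerability checklist) at the 8–18 weeks booking-in visit". No language or literacy item is mentioned.

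Under Intervention outcome measures, the plan for collecting data is: "All data will be collected during face-to-face interviews in the woman’s home, unless otherwise requested". It continues: "In the event of respondents having low levels of literacy, the researcher will administer questions orally".

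Under Recruitment and informed consent, midwives first determine eligibility with the checklist and tell eligible women about the study. Then: "They will also provide eligible mothers with accessible, written information and inform them that a specialist nurse may telephone them". A senior nurse later telephones to confirm eligibility, and a researcher explains the study at the baseline home visit.

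The first primary outcome is "Recruitment as a percentage of eligible participants". Under Study outcome measures, the midwives' screening tools and the senior nurse's records are used "to estimate the number of women eligible for the trial and the percentage recruitment rate".

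**The concern.** Speaking a language and reading it are different abilities. A woman can be fluent in English and read poorly, and as written she meets the indicator for a criterion she does not meet in substance. Elsewhere the plan treats low literacy as compatible with taking part, because an interviewer can ask the questions.

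This matters more in a pilot than in most trials. The first primary outcome is a proportion whose denominator is the number of eligible women, and it is meant to inform the duration and number of sites of a later RCT. If staff cannot tell from the criterion whether a fluent woman with reading difficulty is eligible, that proportion is not well defined. To the extent that such women are turned away, the pilot also learns less about whether oral administration works, although acceptability of the outcome measures is a listed secondary outcome.

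**Working it through.** The plan states no figure on this point, so there is nothing to reproduce. The check compares the sections and then asks what could follow for the recruitment rate.

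**Step 1: criterion against indicator.** The criterion is insufficient spoken English for the intervention arm. The indicator is difficulty reading the information sheet. Four cases arise:

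- Speaks and reads English adequately: eligible on both.
- Lacks English and cannot read the sheet: excluded on both.
- Speaks English adequately but reads poorly: eligible on the criterion, excluded on the indicator.
- Reads adequately but cannot converse: excluded on the criterion, passed by the indicator.

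The third case is the one that the oral-administration provision has in view.

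**Step 2: order of events.** (a) The midwife applies the vulnerability checklist. (b) Women found eligible hear about the study and receive the sheet. (c) The senior nurse telephones to confirm eligibility. (d) The researcher visits for consent and baseline data. Reading difficulty can first show at (b), after the woman has been called eligible. A telephone call at (c) can test spoken English but does not naturally show reading. The denominator draws on records from both (a) and (c), and the article does not say how to classify a woman whose difficulty shows in between.

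**Step 3: consequence for the rate.** Among women who speak adequate English and are otherwise eligible, let s be the share with reading difficulty, p the consent rate in the others, and q the consent rate that women with reading difficulty would have if admitted.

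- Criterion based on speech: R0 = (1 − s)p + sq.
- Excluded and removed from the denominator: RA = (1 − s)p / (1 − s) = p, so RA − R0 = s(p − q).
- Excluded but left in the denominator: RB = (1 − s)p, so RB − R0 = −sq.

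The documents give none of s, p or q. The values below are assumptions chosen only to show the sign, with p = 50%:

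| s | q | R0 | RA | RB |
|---|---|---|---|---|
| 10% | 50% | 0.90×0.50 + 0.10×0.50 = 50.0% | 50.0% | 0.90×0.50 = 45.0% |
| 10% | 25% | 0.90×0.50 + 0.10×0.25 = 47.5% | 50.0% | 45.0% |
| 20% | 50% | 0.80×0.50 + 0.20×0.50 = 50.0% | 50.0% | 0.80×0.50 = 40.0% |
| 20% | 25% | 0.80×0.50 + 0.20×0.25 = 45.0% | 50.0% | 40.0% |

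With equal consent and removal from the denominator there is no distortion. With lower consent and removal, the reported rate is too high. If the women stay in the denominator, it is too low whenever q exceeds zero. The sign depends on a counting rule and a consent rate that the article does not supply.

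**The case against.** The strongest reply is that the criterion governs and the parenthesis only illustrates it. A fluent speaker is not unable to speak sufficient English, the oral-administration sentence shows that low literacy was to be accommodated, and sensible staff would apply the rule that way. This reading is possible, but the text does not state it, and the parenthesis is the only operational rule given. The wording still needs repair.

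A reader might infer that the two provisions cannot both be followed, or that the plan expects to enrol low-literacy women. The documents do not support either. The oral-administration sentence is a contingency and forecasts no number. The written information is described as accessible, whereas the measures include a 36-item stress index, so a woman could manage the sheet and still need questions read to her. The provisions are in tension, but the exclusion does not empty the other of effect.

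A reading test might be defended if the programme relied on written material. The article does not say whether it does, and the criterion as worded concerns speech.

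The inclusion and exclusion criteria are also among the feasibility issues under test, professionals will be interviewed about recruitment materials, and details of decliners will be recorded. These provisions may bring the problem to light. A woman excluded for reading difficulty is not a decliner, however, and the characteristics named for comparing women approached with those recruited are age, parity and reasons for social complexity, not literacy.

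Finally, an article may leave screening detail to the full protocol. That covers how exclusions are logged. It does not cover a rule that the article itself states with a mismatched indicator.

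**Conclusion.** The point holds in a limited form. The language exclusion names one ability and is identified by another, so fluent English speakers with low literacy can be excluded as written. This sits awkwardly with the provision for oral administration. Separately, the sequence of screening, information sheet and eligibility call leaves it unclear whether such women count in the denominator of the primary recruitment rate.

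A reader might infer that the recruitment and retention rates are therefore inflated. The documents do not support that. Inflation of the recruitment rate needs these women both to be removed from the denominator and to be less willing to consent than others; neither is stated. For retention, the denominator is women randomised, and the article does not say whether women with low literacy would be followed up more or less successfully. Size and direction are undetermined for both outcomes, and the table above illustrates the sign only.

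The defect does not invalidate the pilot. It should be corrected because it affects who is eligible in a study whose first primary outcome is recruitment among eligible women.

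**What to change.** - Define the exclusion as inability to understand and converse in spoken English, and drop reading difficulty as the indicator.
- Judge it in the eligibility telephone call that the senior nurse already makes.
- Allow the information sheet and consent form to be read aloud.
- Log language exclusions separately from reading difficulty, and keep women whose only problem is reading in the eligible denominator.

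Recruitment began in April 2016. If it is already complete, report how the criterion was applied and how many women, if any, were excluded for reading difficulty, state whether they were counted as eligible, and correct the criterion for phase 3.

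The cost is one reworded criterion, one extra field in the screening record and a few more minutes at consent for some women. No new staff or additional contact is needed.
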